#### Sleep Diaries

Sleep diaries are an extremely helpful tool to assess sleep patterns (Carney et al., 2012). We adapted a model of a diary and each page contains questions about children’s sleep for each day, forming a booklet that will be answered by the parents over 10 days. It will provide information about: (1) sleep and wake-up times, (2) sleep latency (amount of time taken from bedtime until the child falls asleep), (3) number of awakenings during the night, (4) total sleep time, and (5) naps timing and duration. Additionally, it was included questions on: activities before bedtime, how the child woke up and why; and parent’s perception of wellbeing of their child after each night of sleep. These measures will be registered over the 10 nights, allowing the researchers to examine the children’s habitual sleep patterns in weekdays and weekend.

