Upon enrolment, the four stages of research will be followed, counting on the participation of children and their parents/guardians. All encounters with parents/guardians will happen at 6:40 pm, after the children’s classes, due to the parent’s convenience. First, during the stage of pre-intervention, questionnaires and scales will be applied to assess sociodemographic data, and characterize sleep habits and sleep pattern, by filling out the UNESP sleep habits and hygiene scale (child version) and sleep diary, besides giving the actiwatch to be wore by the children. Parents will also answer the Sleep Disturbance Scale for Children to identify the presence of sleep disorders. After this, parents from experimental group will participate in a workshop conducted by the research team about sleep habits and the importance of healthy sleep in childhood. The team will be available for an additional encounter 1 week after evaluation to clarify doubts about filling in the sleep diary and/or use of actiwatch.

The children themselves will be active in the evaluation steps. All evaluations with them will occur on the first Monday after each meeting with parents, once research begins with the parent’s authorization. In this stage, the children will answer the Pictorial Sleepiness Scale of Maldonado to evaluate sleepiness levels and will characterize their bedroom and the activities that they do before sleep at night, using, respectively, the strategies “Set up your bedroom” and “Mapping activities before bedtime.”

After pre-intervention evaluation, the experimental group will be submitted to the intervention with our serious game “Perfect Bedroom: learn to sleep well,” which will be conducted by three researchers during the children’s classes, at 02:00 pm on Tuesdays and Thursdays (see section “Intervention”).

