The control group will follow the institution’s school activities defined on the school schedule. The only moments of contact with study staff will be during evaluation, pre-, post and following intervention, to assure a proper control condition, in accordance to our research question about intervention works (Holmes et al., 2018). Considering this, further control will be needed for the following factors: contact with research team limited only to evaluation periods to avoid confusing factors such as attention, warmth, or human relationships. In the evaluation stages, the guardians will answer questionnaires and scales to assess sociodemographic and health data, sleep habits and sleep pattern of their child. The children themselves will answer: a scale to assess sleepiness levels, a questionnaire to evaluate the serious game and the game itself, will characterize their bedroom and the activities they perform before sleep. Also, teachers will be informed only essential information about the study and will be instructed to not use the knowledge acquired about sleep in class during the period of the research.

After completion of the intervention, the last two steps, post intervention evaluation and follow-up evaluation, will be conducted after 4 weeks. In these stages sleep habits and sleep patterns will be re-evaluated by the parents. Additional encounters 1 week after each evaluation will be provided to clarify any doubts about filling in the sleep diary and/or use of actiwatch. During these steps the children will be required to answer the Pictorial Sleepiness Scale of Maldonado and to characterize their bedroom and any activities that they perform before sleep at night (**Figure 2**). Thus, there will be three meetings with parents/guardians during evaluation steps, with three more other encounters to elucidate any doubt about assessments. Missing data will result in individuals being excluded without outcome.

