Presence of electronic media in the bedroom (e.g., television, video game, and computer) and the use of them next to bedtime are related to late bedtime and decreased sleep duration. In addition, children that sleep next small screens (e.g., smartphones) relate impacts in perception of insufficient rest, probably caused by waking up due to notifications on the small screen (Cain and Gradisar, 2010; Falbe et al., 2015). The opposite is also true, and children that do not have electronics in the bedroom report more hours of sleep. Other factors related to the bedroom are also relevant, such as providing a comfortable bedroom and conditions to sleep, but this is challenging for families of low SES (Chung et al., 2014; Bagley et al., 2015).

Our serious game includes recommendations in sleep environment, but just the game is not enough to help children in families with low-incomes. Provide conditions, such as quiet and dark bedroom and comfortable bed, depends on the neighborhood that the families live and their incomes. Thus, subsequent interventions should include actions to help these families provide a comfortable bedroom, such as Time’s Beds for Kids in EUA (Mindell et al., 2016).

It stands-out that in Brazil did not exist, in our knowledge, any questionnaire adapted and validated to evaluate the chronotype of children with ages between 7 and 8 years, as different types have influences on the presence of sleep disorders and accentuate inadequate sleep habits (Jafar et al., 2017), so chronotype influence was not assessed in this protocol.

Other pitfall that could be noted, is the consideration that parent’s reports may be influenced by social desirability, indicating good sleep hygiene practices instead of the real situation. Another important challenge is to promote parental involvement, since previous researches indicated a decrease in participation over the evaluation periods (Jones et al., 2013; Wilson et al., 2014; Mindell et al., 2016). In this way, we proposed follow-up meetings with parents to minimize this decrease on participation.

Although in this protocol efficacy measures in evaluation will be limited to sleep habits and patterns, the promotion of optimal sleep has consequences in multiples domains (e.g., cognitive, health, temperament) that are sometimes completely forgotten in sleep programs interventions (Blunden, 2017). Thus, future studies should include other outcomes to evaluate efficacy, such as cognitive and academic performance.

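### Only experimental-arm parents attend a sleep-habits workshop, so the trial cannot isolate the effect of the game, and the undated workshop may overlap baseline recording

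*Protocol article*

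**What the plan says.** The Introduction and the opening of Design and Procedures state the aim as the effect of playing the game on sleep habits and sleep parameters. The Abstract and the intervention section describe the intervention as six 50-minute game sessions over three weeks and do not mention a parent workshop.

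Design and Procedures, in its account of the pre-intervention stage, says: "After this, parents from experimental group will participate in a workshop conducted by the research team about sleep habits". The game sessions follow in a later paragraph.

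For controls, the same section limits staff contact to the evaluations and gives the reason: "contact with research team limited only to evaluation periods to avoid confusing factors such as attention, warmth, or human relationships". Teachers are told not to use sleep knowledge in class during the study, and their own sleep workshop waits until all evaluations are over. Under the Ethics Statement, controls receive the intervention after all evaluations.

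The Abstract names sleep habits as the primary outcome and sleep parameters as secondary. Parents complete the UNESP habits and hygiene scale, the Sleep Disturbance Scale and the diary. Intergroup and Intragroups Analysis compares the arms at each of three time points by t-test or chi-square, once baseline homogeneity has been confirmed. It also calculates post-minus-pre differences and percentage change.

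**The concern.** Two components, the game and the parent workshop, go to one arm and neither goes to the other. A positive result would be reported as an effect of the game although parent education alone might have produced it. The article's own background makes that plausible: it cites a parent-directed campaign followed by fewer bedroom electronics and longer night sleep, and a parent brochure that improved knowledge and intentions to change habits.

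The workshop could also change how parents answer. Anticipated Results concedes that parents' "reports may be influenced by social desirability, indicating good sleep hygiene practices instead of the real situation". Parents in one arm only will have been taught by the research team about sleep habits before they complete the post-intervention scale and diary.

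Timing is a second issue. If the workshop comes before baseline recording ends, some experimental-arm baseline values are no longer untreated values.

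**Working it through.** **1. What the contrast estimates.** Let G be the effect of the game, W the effect of the workshop on the child's sleep, and R the shift in parental reporting caused by the workshop.

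- Parent-reported outcomes: experimental minus control = G + W + R, plus any interaction.
- Actigraphy: experimental minus control = G + W, plus any interaction.

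Workshop and game coincide exactly with arm. There is one contrast and at least two unknowns, so no test in the analysis section can recover G. Actigraphy removes R but not W. This step does not depend on when the workshop takes place.

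**2. How large W would need to be.** Inputs from Participants: alpha 5%, effect size 0.5, power 95%, 88 per group.

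The plan's figure first. The normal approximation is n = 2(z_alpha + z_power)² / 0.5².

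- One-sided: 2(1.645 + 1.645)² / 0.25 = 86.6, so 87; the t-based calculation gives 88, as stated.
- Two-sided: 2(1.960 + 1.645)² / 0.25 = 104.0, so 104; the t-based calculation gives 105.

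The stated 88 thus reproduces as a one-sided test. That is a separate matter and nothing below rests on it.

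The documents give no workshop effect, so W is assumed to be 0.1 to 0.3 SD. With G = 0, the noncentrality is W × √(88/2) = 6.633 W:

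| Assumed W (SD) | Noncentrality | P(significant), two-sided 5% | One-sided 5% |
|---|---|---|---|
| 0.1 | 0.66 | 0.10 | 0.16 |
| 0.2 | 1.33 | 0.26 | 0.37 |
| 0.3 | 1.99 | 0.51 | 0.63 |

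**3. Where the workshop falls.** No date is given. The sequence in Design and Procedures is:

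- "First, during the stage of pre-intervention, questionnaires and scales will be applied to assess sociodemographic data", together with the sleep scales;
- the diary, and "besides giving the actiwatch to be wore by the children";
- the workshop, introduced by the words that open the quote on it;
- an encounter one week after the evaluation to clear up doubts about the diary and actiwatch;
- the children's own baseline tasks, on the first Monday after the parent meeting.

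Sleep Diaries describes the pages as "forming a booklet that will be answered by the parents over 10 days", and Actigraphy has the device worn over the same 10 days. A clarification encounter at day 7 makes sense only if recording is still under way. If recording starts at the meeting, a workshop that evening precedes all 10 nights and the children's tasks. A workshop at day 7 precedes about 10 − 7 = 3 nights. A workshop after day 10 precedes none.

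**4. What a shifted baseline would do.** On this reading the UNESP and Sleep Disturbance scales are answered before the workshop, so their baselines are unaffected. Exposed are the diary, actigraphy and probably the children's sleepiness, bedroom and activity tasks. If a shift of 0.1, 0.2 or 0.3 SD is already present in such a baseline variable:

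- its homogeneity t-test is significant with probability 0.10, 0.26 or 0.51, against 0.05 with no shift;
- a true total effect of 0.5 SD appears as a difference in change of 0.5 − 0.1 = 0.4, 0.5 − 0.2 = 0.3 or 0.5 − 0.3 = 0.2 SD. If changes were compared between arms, with the same SD, two-sided power would be 0.75, 0.51 or 0.26, against 0.91 at 0.5 SD.

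The two mechanisms pull in opposite directions: the workshop can inflate the post-intervention contrast, while a shifted baseline shrinks the change.

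**The case against.** The best defence is that the game is described as the main, not the only, resource of the intervention, and that a no-intervention control is a declared choice. On that view the trial tests a package and needs only clearer wording. This stands in part: rewording is one acceptable remedy. But the hypothesis and aim name the game alone, and the article delays the teachers' workshop until after all evaluations.

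Four stronger readings may tempt a reader, and the documents do not support them.

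- *The baseline is contaminated as a matter of fact, and allocation is disclosed before baseline is complete.* Both rest on an inferred date. The flow chart is not shown, and the workshop follows a list that includes filling out the diary, so it could come after the diary is complete. The meeting count does not settle this: "there will be three meetings with parents/guardians during evaluation steps, with three more other encounters to elucidate any doubt about assessments" covers evaluations and clarification, and a workshop is neither. The baseline of the parent habits scale is not affected on either reading.
- *Part of the treatment effect is lost from the main comparison.* The planned between-group tests compare the arms at each time point. A baseline shift does not shrink the post-intervention or follow-up contrasts; it affects only the change measures and the homogeneity check.
- *The 30-minute gain in sleep duration cited in the Introduction measures the possible bias.* That programme also taught teachers and pre-school children, so it says little about a parent workshop alone.
- *The six game sessions are themselves an attention confounder that contradicts the contact rule.* The rule stands in the description of the control condition. Objecting to the sessions is objecting to the disclosed no-intervention control.

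**Conclusion.** The attribution problem holds with high confidence and follows directly from the text. As written, the trial estimates game plus parent workshop versus no intervention, and would report the result as the effect of the game. The article does not allow the size to be determined. The probabilities of 0.10 to 0.51 for a significant result with an inert game rest on an assumed workshop effect of 0.1 to 0.3 SD, 88 analysed per group, independent observations and a two-sided test.

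The timing problem is conditional, with moderate confidence. The order of the text and the one-week encounter point to a workshop before the baseline diary and actigraphy are complete, but no date is stated. If that reading is right, the exposure is limited to the diary, actigraphy and probably the children's baseline tasks, and acts through the change measures and the homogeneity check.

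**What to change.** Choose one of the following, and state the date of the workshop relative to baseline recording in either case.

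1. **Equalise the arms.** Give the identical workshop to parents of both arms, or defer it until after the last follow-up, as is already planned for teachers. A workshop for both arms costs one more evening session and may reduce the between-group contrast, because the comparison becomes the game on top of parent education. Deferral may lower parental engagement, which Anticipated Results names as a challenge.
2. **Keep it in one arm and change the claim.** Hold the workshop only after baseline diaries and actiwatches have been returned and the children's baseline tasks are done. Describe it as part of the intervention in the Abstract and intervention section, and restate the hypothesis and conclusion as game plus parent workshop versus no intervention. The cost is a narrower claim: the trial could no longer speak for the game alone.

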### Design and Procedures

It will be used an experimental, prospective, quantitative and randomized controlled trial to compare effects of game application on change of habits and parameters of sleep, besides what the users will be able to do by playing this serious game. In order to achieve that, the following steps will be conducted: (1) randomization of participants to allocate each one in experimental or control group; (2) use of a control group that should not be submitted to intervention, to infer highest internal validity; (3) intervention with experimental group, which will allow us to evaluate if there was any modification in the parameters evaluated, determining the validity of the intervention and (4) evaluation of participants at three distinct moments throughout the study, namely: pre-intervention, immediate post-intervention and follow-up assessment, after 4 weeks (Suresh, 2011).

After selecting the schools by convenience, experimental and control groups are selected by two processes of randomization. The first will select which classes will compose the experimental and control groups in each school, throughout a basic method of randomization that is flipping a coin; in other words, one situation will be associated with each side of coin (e.g., heads – control and tails – experimental) to determinate the assignment of each class. Second, the function “Randomly assign subjects to groups” in online software GraphPad^1^ will be used to allocate participants of each class with valid data for analysis to each group.

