The second component of the serious game are four boards representing the floor of the bedroom that the children will assemble. In addition, to be more interesting and dynamic we included bonus cards (e.g., Congratulations, you do not use your cell phone before bedtime. Take out two more Perfect Bedroom Cards!) and surprise cards (e.g., You have television and computer in your room. These objects hinder the beginning of sleep! Pass the turn!). To allow the players to buy the items that will compose the bedroom bank notes with values of 1 and 2 were created. Available for the children to buy with the notes are 32 objects, divided in eight types (lamp, pillow, bed, chair, window, table, wardrobe, and fan), with four different colors (pink, yellow, green, and blue), to assemble the ‘perfect bedroom’ without electronics devices. The last pieces of the game are cards that list the objects that can be purchased and their values.

To play, all participants will receive the necessary materials described, with the starting player randomly chosen. The first participant will draw a card from the perfect room cards deck, which contains adequate (positive cards) and inadequate (negative cards) sleep habits, bonus or surprise cards. After drawing one card the player must do the card indicates. The player who wins is the one who assembles the perfect room first, with all the items on the list, or the one with the most objects in their board.

The intervention will be conducted by three previously trained researchers. It will occur at the children’s school, twice a week (on Tuesdays and Thursdays), starting at 02:00 pm, for 3 weeks in a row, resulting in six sessions of 50 min each. In each session players will be challenged to set up the “perfect bedroom.” They will apply the behavioral and environmental changes of sleep hygiene to promote healthy sleep.

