### Intergroup and Intragroups Analysis

Once confirmed that the groups did not present significative differences, the comparison procedure will be conducted. Variables included in sleep patterns (sleep latency, sleep efficiency, sleep and waking up times, total sleep time), sleep hygiene and sleep problems will be considered dependent variables and will be compared between experimental and control groups, during the three points in time where they will be evaluated, using independent student’s *t*-test and chi-square (χ^2^) with odds ratio and dimension of association (Phi and Cramer’s V), depending on the nature of the data. It will allow us to identify if the intervention with the serious game yielded improvements in objective sleep measures and sleep hygiene.

To evaluate possible improvements intragroup, comparisons will be conducted using: ANOVA (F) for repeated measures with Bonferroni’s post test and Q Chochran test. For all numeric variables percentage will be calculated with delta differences (post-test score minus the pre-test score) and percentage’s change [(post-test score) minus (pre-test score) divided by (pre-test score) multiplied by 100]. These measures will allow us to evaluate the intervention’s immediate effects and the maintenance of this effect after 4 weeks.

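### Limiting the control group's contact with researchers does not avoid attention effects: it makes researcher contact differ by arm, so a difference belongs to the whole package and not to the game alone

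*Protocol article*

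**What the plan says.** All references are to the protocol article.

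- **Control condition (Design and Procedures).** "The control group will follow the institution’s school activities defined on the school schedule". Staff contact is restricted: "The only moments of contact with study staff will be during evaluation, pre-, post and following intervention, to assure a proper control condition". The same paragraph then says that further control is needed, and gives as the measure "contact with research team limited only to evaluation periods to avoid confusing factors such as attention, warmth, or human relationships".
- **Experimental condition (Design and Procedures; Intervention With Serious Game).** The game is delivered in sessions "which will be conducted by three researchers during the children’s classes, at 02:00 pm on Tuesdays and Thursdays", "for 3 weeks in a row, resulting in six sessions of 50 min each". In addition, "parents from experimental group will participate in a workshop conducted by the research team about sleep habits and the importance of healthy sleep in childhood".
- **Inference.** Design and Procedures sets out to compare the effects of applying the game and justifies the comparator as "use of a control group that should not be submitted to intervention, to infer highest internal validity". Intergroup and Intragroups Analysis says of the between-group comparison: "It will allow us to identify if the intervention with the serious game yielded improvements in objective sleep measures and sleep hygiene".
- **Limitations (Anticipated Results).** Social desirability in parents' reports is named as a pitfall. Unequal researcher contact between the arms is not mentioned.

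**The concern.** A non-specific factor such as attention is controlled when both arms receive it to the same degree. Withholding it from one arm makes it part of the contrast. The article presents the withholding as protection against confounding, which reverses its effect.

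What is at stake is the conclusion. The untreated comparator can show whether children given the intervention differ from children in ordinary lessons. If the article's rationale is taken at face value, a difference would be read as due to the game and its sleep-hygiene content, with attention ruled out. Anticipated Results also suggests that the game could be used at home under parental supervision. That setting removes the researchers, so it relies on an effect of the game alone.

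**Working it through.** **1. Contact received by each arm**

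| Component | Experimental | Control | Source |
|---|---|---|---|
| Staff contact at the three evaluations | Planned | Planned | Design and Procedures |
| Researcher-led sessions with children | 2 per week x 3 weeks = 6; 6 x 50 min = 300 min | 0 min | Intervention With Serious Game |
| Content of those sessions | The game | Usual school activities | Design and Procedures |
| Parent workshop before the intervention | Yes (duration not given) | No | Design and Procedures |

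The difference in scheduled researcher contact with children outside evaluations is 300 - 0 = 300 minutes.

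**2. What the planned comparisons estimate**

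Let g be the effect of the game and its content, a the effect of the extra researcher contact, and w the effect of the parent workshop. Assume for simplicity that they add. Every experimental child is assigned all three components and every control child none. Then:

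expected between-group difference = (g + a + w) - 0 = g + a + w

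The planned t-tests and chi-square tests estimate this sum at each time point. No group receives a without g, so nothing in the data separates them. The repeated-measures ANOVA and Cochran Q tests do not help: within the experimental arm they estimate g + a + w plus any change over time. If the workshop were dropped or given to both arms, w would leave the contrast but g + a would remain.

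**3. An illustration under a stated assumption**

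The documents give no value for a or w, so the following only shows what could happen.

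- The plan's figure first: a standardised effect of 0.5, alpha 5% and power 95% give 87.26, rounded up to 88 per group, with a one-sided two-sample t-test. This reproduces the stated 88. (A two-sided test would need 105. That is a separate matter.)
- Now suppose g = 0 and the non-specific effect (a + w) is d standard deviations. With 88 independent children per arm, the noncentrality is d x sqrt(88/2) = 6.633d. The chance of a two-sided p < 0.05 is then:

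| Assumed d | Noncentrality | Chance of a significant difference |
|---|---|---|
| 0.2 | 1.33 | about 26% |
| 0.3 | 1.99 | about 51% |
| 0.5 | 3.32 | about 91% |

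In each row the game does nothing, yet a significant difference would be open to being credited to it.

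**The case against.** **The comparator is a declared and legitimate choice.** The Abstract names a no-intervention group, and Design and Procedures links the control condition to the question of whether the intervention works. Usual activity is a proper comparator for that question. This stands, and it is why no new arm is asked for.

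**The sentence may mean only that controls should be kept free of non-specific intervention.** That reading fits the paragraph, and the article never says that attention is equal between arms. But the sentence is offered as a further control that avoids confounding factors, and under either reading the design lacks that property.

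**The analysis section speaks of the intervention with the game, and the game is called its main resource.** This partly describes a package already, so the over-attribution is one of degree. The aim in Design and Procedures is looser, and nothing in the article tells the reader that the conclusion stops at the package.

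**A reader might infer that the session leaders also collect the children's self-reports, so that children answer to please familiar adults.** The documents do not support this. Three trained researchers run the sessions, but the article does not say who administers the sleepiness scale or the sticker tasks. It also discards the first day of sleepiness data to reduce the effect of a new person in the classroom. The point does not depend on any such overlap.

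**A reader might infer that all contact is confounded with arm.** That is too strong, because both arms meet staff at the evaluations. Only the contact beyond them differs.

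**Conclusion.** The concern holds in a limited form. The stated safeguard against attention effects is not a property of this design: outside evaluations, scheduled researcher contact with children is 300 minutes against 0, and it coincides with arm. The contrast supports a conclusion about the whole package against usual school activities. It does not support a conclusion about the game or its sleep-hygiene content alone.

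The 300 minutes assume that the sessions run as scheduled. The probabilities in the illustration rest on assumed effect sizes and independent children; they do not estimate bias in this trial. The documents cannot say what share of a difference attention would explain.

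It would be tempting to conclude that the trial is uninformative, or that the planned actigraphy could settle the matter. Neither follows. The package comparison is a fair question, and if attention changes sleep, actigraphy would move as well, so agreement with it would not isolate the game.

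**What to change.** Three changes of wording in the protocol:

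1. In Design and Procedures, delete the statement that limiting contact to evaluations avoids effects of attention, warmth or relationships. The restriction itself can stay, described as part of a usual-activity control.
2. In the aim and in Intergroup and Intragroups Analysis, restate the comparison and the permitted conclusion as the whole package against usual school activities. The package is six researcher-led game sessions plus, if it is kept, the parent workshop given only to the experimental arm.
3. In Anticipated Results, add the limitation that effects specific to the game or its sleep-hygiene content cannot be separated from researcher attention.

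No new data, arm or test is needed. The cost is a narrower claim about the game, and the suggestion of home use would have to be worded as untested by this comparison.
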